## Methods/design

Here we present our two-phase study, shown in Fig. 1. In phase 1, we aim to have the Visual impairment in Parkinson’s Disease Questionnaire (VIPD-Q) completed by at least 750 PD patients and 250 healthy controls. In phase 2, a subgroup of responders (*n* = 100) will be invited for an extensive neurological and ophthalmological assessment. The study is performed at three study sites (Radboud University Nijmegen Medical Centre, the Netherlands; the Medical University Innsbruck, Austria; and The OLVG hospital Amsterdam, the Netherlands). Each centre obtained local ethical approval (NL58535.091.16;AN2016–0181).The study will be performed in accordance with the Declaration of Helsinki. All participants have to give written informed consent prior to participation. This study is registered in The Dutch trial register: NTR 7663.

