### Phase 2: neurological and ophthalmological assessment

#### Patient collective and recruitment

From the responders of phase 1, a sample of 100 patients will be invited for a full clinical and ophthalmological assessment. Patients will be selected based on their scores on the VIPD-Q aiming to include 70 patients with and 30 patients without visual impairment, which is operationally defined as patients scoring the highest 30% or the lowest 30% on the screening questionnaire, respectively. Due to personnel capacity, a sample of 30 patients in the Netherlands (10 in the lowest 30% and 20 in the highest 30%) and 70 patients in Austria (20 in the lowest 30% and 50 in the highest 30%) will be selected and invited for the clinical and ophthalmological assessment. The OLVG hospital only participated in phase 1 of this study. Inclusion and exclusion criteria are described in Table 2. Selection will start after at least 250 questionnaires have been completed. (See Fig. 1).

**Table 2 Tab2:** Inclusion and exclusion criteria

Inclusion criteria	Exclusion criteria
Diagnosis of PD according to the UKPDSBB criteria	Hoehn and Yahr Parkinson’s staging score ≥ 4
The patient must be able and willing to give written informed consent	Secondary cause of parkinsonism as detected by history (e.g. drug-induced parkinsonism)
The patient must be willing to participate in all study related activities and visits	Secondary cause of parkinsonism as detected by investigation (e.g. vascular parkinsonism as detected by neuroimaging)
Age of onset Parkinson’s disease > 30 years	Dementia according to DSM-IV
Stable doses of Parkinson medications ≥4 weeks	Major depressive disorder according to DSM-IV
Current age ≥ 60 years	Psychotic disorder(s) according to DSM-IV
	Prior brain surgery (except deep brain stimulation)
	Previous eye surgery (except phacoemulsification for cataract and artificial lenses)
	Blindness in 1 eye
	Medication that influences normal visual function other than PD medication. (Detailed information, please see Additional file 2: Appendix 2)
	Systemic diseases that may cause eye problems (HIV, DM type I, type II if the patient had ophthalmologic therapy and/or abnormalities at last screening)
	Neurodegenerative diseases other than Parkinson’s disease
	History of lesions near the optic chiasm or occipital cortex
	Migraine

Inclusion and exclusion criteria of the Visual Impairment in Parkinson’s Disease study

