
### Statistical analysis plan

95% Confidence intervals, means, standard deviations and frequency distributions will be calculated for all outcomes. Nonparametric variables (age, disease duration, LED, total score VIPD-Q) will be expressed as the median, interquartile range (IQR), minimum, and maximum. To compare groups, we will use the student’s t-test for parametric continuous variables and the Mann-Whitney U test for non-parametric continuous variables. All analyses will be performed with SPSS 22.0 (SPSS Inc., IBM, Chicago, IL, USA).

To address the first study objective (validity of the screening questionnaire), we will compare the results of the VIPD-Q with the ophthalmological assessments using analysis of intraclass correlation coefficient (ICC), with Cohen’s kappa. The results of the ophthalmological assessments will be categorized in visual disorders within the domains of the VIPD-Q (ocular surface, intra- ocular, oculomotor and optic nerve). We hypothesize moderate to good correlation (ICC > 0.5) between the scores on the domains based on the ophthalmological tests and the scores on the domains based on the screening questionnaire. We will also address correlation for the total score. In addition, we will calculate optimal cut-off points of the domains and total score of the VIPD-Q using the receiver operating characteristic (ROC).

For the second and third objective (determine the prevalence and severity of visual problems in PD; impact on clinical functioning), PD patients will be compared with healthy controls using chi-square-tests for categorical values (sex, education, co morbidity, visited ophthalmologist, visual aid, vision changes during the day, difficulties with daily activities, impact on quality of life) or Mann-Whitney U test for non-parametric continuous variables (age, total score VIPD-Q, score per domain). Furthermore, the relationship between falling, disease duration, MDS-UPDRS, hand-eye dexterity, gait and balance tests, and visual problems will be assessed using multiple linear regression analysis.

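### Student's equal-variance t-test is named for group comparisons although the phase 2 groups are 70:30 by design; Welch's test would be a nearly free improvement for supporting comparisons of means

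*Protocol article*

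**What the plan says.** The section *Statistical analysis plan* of the protocol article has one general sentence on comparing continuous variables between groups: "we will use the student’s t-test for parametric continuous variables" and "the Mann-Whitney U test for non-parametric continuous variables". It names no variable and no contrast for the t-test, and it does not mention the variance assumption.

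The same section says which variables are treated as non-parametric: "Nonparametric variables (age, disease duration, LED, total score VIPD-Q) will be expressed as the median". The questionnaire's domain scores join that list in the paragraph on the second and third objectives.

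The group sizes in phase 2 are set under *Patient collective and recruitment*: "aiming to include 70 patients with and 30 patients without visual impairment". These are operationally the highest and lowest 30% of questionnaire scores. The split by country agrees with this: 20 + 50 = 70 high scorers and 10 + 20 = 30 low scorers.

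Many of the continuous measures not declared non-parametric belong to the phase 2 battery in Table 3, which is given to patients only. Examples are visual acuity, contrast score, corneal thickness and retinal thickness.

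**The concern.** Student's t-test estimates one common variance from both groups. With equal group sizes this does little harm even when the true variances differ. At 70:30 the pooled variance is dominated by the larger group, while the uncertainty of the difference is driven largely by the smaller group. If the larger group is more variable, the standard error is too large and power is lost. If the smaller group is more variable, the standard error is too small and false positives rise.

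Unequal spread is plausible here. The two groups come from opposite ends of a symptom score, and high scorers may have disorders in any of four anatomical domains. Calling a variable parametric describes the shape of its distribution and does not establish equal variances.

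At stake is the accuracy of p-values and confidence intervals for any phase 2 comparison of means between the two groups.

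**Working it through.** **Inputs from the article.** Group sizes are n₁ = 70 and n₂ = 30. The test is Student's t-test.

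**Assumptions.** The two-sided level is 0.05 (the article states 95% confidence intervals but no test level), and data are normal. The SD ratio r is the SD of the smaller group divided by that of the larger. The article gives no SDs, so r is varied. It also gives no power or error calculation, so there is no stated figure to reproduce.

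**Formulas.** Set the SD of the larger group to 1.
- True variance of the difference: V_true = 1/70 + r²/30
- Variance the pooled test uses, on average: V_pool = [(69 + 29r²)/98] × (1/70 + 1/30)
- Standard error ratio: k = √(V_pool/V_true)
- Approximate true error: 2 × [1 − Φ(1.984 × k)], where 1.984 is the critical t value on 98 degrees of freedom

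**Worked case, larger group more variable by 1.5 (r = 0.67).**
- V_true = 0.01429 + 0.4489/30 = 0.02925
- V_pool = (82.02/98) × 0.04762 = 0.03985
- k = √(0.03985/0.02925) = 1.167, so the standard error is about 17% too large
- Approximate error 2.1%

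**Worked case, smaller group more variable by 1.5 (r = 1.5).**
- V_true = 0.01429 + 2.25/30 = 0.08929
- V_pool = (134.25/98) × 0.04762 = 0.06523
- k = √(0.06523/0.08929) = 0.855, so the standard error is about 15% too small
- Approximate error 9.0%

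**Results, with simulation (40,000 runs per row, 70:30, no true difference).**

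| SD small / SD large | k | Formula | Pooled, simulated | Welch, simulated |
|---|---|---|---|---|
| 0.67 | 1.167 | 2.1% | 2.3% | 5.1% |
| 0.8 | 1.093 | 3.0% | 3.2% | 4.9% |
| 1 | 1.000 | 4.7% | 5.0% | 5.0% |
| 1.25 | 0.915 | 7.0% | 7.2% | 5.0% |
| 1.5 | 0.855 | 9.0% | 9.5% | 5.2% |

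The formula reads slightly low because it treats the statistic as normal. Simulation error near 5% is about 0.1 percentage point: √(0.05 × 0.95/40,000) = 0.0011.

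**Power, simulated at 70:30.** The differences are assumed.
- Equal SDs of 1, difference 0.6: pooled 77.5%, Welch 76.9%. The price of Welch is 0.6 percentage points.
- Larger group SD 1.5, smaller group SD 1, difference 0.7: pooled 66%, Welch 77%.

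**Where the t-test could apply.** The validation objective uses the intraclass correlation coefficient with kappa, and ROC analysis. Patients and controls are compared by chi-square and Mann-Whitney tests. Falls, gait and balance tests and hand-eye dexterity go to multiple linear regression. What remains for the general t-test sentence is any comparison of means on the other phase 2 measures, most naturally between the 70 and the 30.

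**The case against.** The strongest reply is that the article specifies no comparison of means between the 70 and the 30. The t-test appears once, in a general sentence, and no stated objective is tied to it. This stands, and it limits the point to supporting analyses.

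A second reply is that the article never says pooled or equal variances, and that the variance option is a detail a condensed article may leave to the full plan. This stands only in part. The article does name a method, and that name ordinarily denotes the equal-variance test; the unequal-variance form goes by another name. The wording does not stop an analyst from reporting the unequal-variance row in SPSS, but it does not direct the analyst there either. Choosing between the rows by Levene's test would keep the simulated error at 4.0% to 6.3% at 70:30, which is better than pooling throughout but no simpler than naming Welch.

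A third reply is that the SD ratios are not from the document. This stands. If the larger group is the more variable one, the test is conservative and the loss is in power only.

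A reader might also infer that the patient-control comparison is affected, since the questionnaire is to be "completed by at least 750 PD patients and 250 healthy controls". The article does not support that. It says "PD patients will be compared with healthy controls using chi-square-tests for categorical values", and for continuous variables it names "Mann-Whitney U test for non-parametric continuous variables (age, total score VIPD-Q, score per domain". Controls complete only the questionnaire, so they have no phase 2 measurements to compare. Nor do walking or dexterity times serve as examples, because the article assigns those to regression.

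**Conclusion.** The point holds as a modest improvement to a named method. At 70:30, Student's t-test has a true error of about 3% or 7% for a 20 to 25% SD difference, and about 2.3% or 9% for an SD ratio of 1.5, depending on which group is more variable. Welch's test stays near 5% throughout. These figures rest on assumed SD ratios, normal data and a two-sided 5% level.

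It would go too far to say that p-values and intervals are wrong whenever the spreads differ. Size and direction depend on the SD ratio, small differences matter little, and the article gives no SDs from which to tell. It would also go too far to say that a main result is compromised, because none of the analyses spelled out for the objectives is a t-test.

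**What to change.** In the general sentence on group comparisons in *Statistical analysis plan*, replace Student's t-test by Welch's unequal-variance t-test, reported with its own confidence interval, for every two-group comparison of means. This also settles beforehand which of the two SPSS rows is reported.

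The cost is a change of a few words. SPSS prints the result in the same table, in the row labelled *equal variances not assumed*. The power given up when the SDs are equal is under one percentage point. Sample size, data collection and the other analyses are unchanged.

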### Phase 1: screening questionnaire

The VIPD-Q was developed by neurologists and ophthalmologists to detect a broad range of ophthalmologic disorders in PD patients. It is based on an extensive literature study, previous questionnaires, and common and disabling visual disorders in both PD patients and healthy older people [2, 11, 13, 15, 17–34]. The questionnaire includes 22 questions on visual problems, plus a standard set of demographic data (Additional file 1: Appendix 1). Answers are given on a 4-point Likert scale ranging from “never have problems” to “daily problems”, without possibility to give a neutral answer. As a second step, we grouped the questions according to the anatomical location of a visual disorder. These domains were agreed upon by a consensus procedure involving three independent ophthalmologists (one from each study site). They were asked to categorize the questions in four domains (Table 1: ocular surface, oculomotor, intra-ocular and optic nerve). Consensus was reached during a meeting with the three ophthalmologists. Six questions could not be categorized in one domain, but rather indicate the involvement of more than one anatomical domain. The VIPD-Q is designed as a patient self-scoring instrument and takes about 20 min to complete.

**Table 1 Tab1:** Domains and corresponding questions with possible diagnosis

Domains	Issues	Possible diagnosis	Question
Ocular surface	lacrimal fluid, eyelids, conjunctiva, cornea	dry eye disease, blepharitis, blepharospasm, conjunctivitis, low eye blink rate,	1: I have blurry vision, when I read or work on a computer. 2: I have a burning sensation or gritty feeling in my eyes. 3: I have mucus/slime or particles in my eyes or eyelids. 4: I have watery eyes.
Intra-ocular	lens, uvea, macula, retina	diabetic retinopathy, macular degeneration, retinal detachment, hypertensive retinopathy, micro-vascular retinopathy, cataract, refraction errors, glaucoma	5: When I read, some letters disappear. 6: Lines that should be straight, appear to be wavy or blurred. 7: I won’t go out alone in the evening or at night because my night vision is insufficient. 8: When I drive at night, the oncoming headlights cause more glare than before.

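### The validity hypothesis ICC > 0.5 is set between two measures with no stated common scale, so arbitrary scoring can decide whether it is met

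*Protocol article*

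**What the plan says.** The Statistical analysis plan section of the Protocol article says of objective 1: "we will compare the results of the VIPD-Q with the ophthalmological assessments using analysis of intraclass correlation coefficient (ICC), with Cohen’s kappa". On the examination side, "The results of the ophthalmological assessments will be categorized in visual disorders within the domains of the VIPD-Q". The hypothesis follows: "We hypothesize moderate to good correlation (ICC > 0.5) between the scores on the domains based on the ophthalmological tests" and the corresponding questionnaire domain scores. The same comparison is extended to the total: "We will also address correlation for the total score". A further analysis is then announced: "we will calculate optimal cut-off points of the domains and total score of the VIPD-Q using the receiver operating characteristic (ROC").

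On the questionnaire side, the section on phase 1 says "Answers are given on a 4-point Likert scale", running from never to daily problems. Table 1 places four items in each of four domains. Of the 22 items, "Six questions could not be categorized in one domain".

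The article gives no numeric coding of the items, no rule for forming a domain score, no numeric scoring of the examination and no ICC form.

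**The concern.** An ICC asks whether two readings of the same quantity, in the same unit, agree. It is lowered by unequal variances and, in its absolute-agreement form, by unequal means as well. Here one reading is how often a patient notices symptoms. The other is whether, or which, disorders an ophthalmologist finds, using tests recorded in millimetres, seconds, mmHg and centimetres, each with its own cut-off. These are not two readings of one quantity, and the article calls the resulting ICC a correlation, which it is not in this setting. Kappa likewise needs the same categories on both sides, and none are stated for the questionnaire.

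Validation of the VIPD-Q is the study's first aim, and 0.5 is the only number offered for judging it. If the value of the ICC turns on how the two sides happen to be scored, a questionnaire that separates patients well could appear to miss the hypothesis. Equally, a choice of scoring could bring it over the line.

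**Working it through.** The article derives no figure here; 0.5 is a stated threshold, so there is nothing to reproduce. The check asks how the ICC behaves for measures of this kind.

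**Inputs from the article:** four items per domain, four answer levels, 22 items in total, and 100 phase 2 patients (70 high and 30 low scorers).

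**Assumptions:** items coded 0-3, so a domain sum runs 0-12 (4 × 3) and a total runs 0-66 (22 × 3). Domain sum: mean 4, SD 3. Yes/no domain disorder: mean 0.5, SD 0.5. Alternatively, a disorder count: mean 1, SD 1.

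**Formulas** (two measures, correlation r, SDs s1 and s2, means m1 and m2; the second is the large-sample form):
- Consistency ICC = 2·r·s1·s2 / (s1² + s2²)
- Absolute-agreement ICC = 2·r·s1·s2 / (s1² + s2² + (m1 − m2)²)

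| Assumed scoring | r | Consistency | Absolute agreement |
|---|---|---|---|
| Item sum vs yes/no | 0.7 | 2.1/9.25 = 0.23 | 2.1/21.5 = 0.10 |
| Item sum vs yes/no | 1.0 | 3/9.25 = 0.32 | 3/21.5 = 0.14 |
| Item sum vs disorder count | 0.7 | 4.2/10 = 0.42 | 4.2/19 = 0.22 |
| Item sum vs disorder count | 1.0 | 6/10 = 0.60 | 6/19 = 0.32 |
| Item mean (mean 1, SD 0.75) vs yes/no | 0.7 | 0.525/0.8125 = 0.65 | 0.525/1.0625 = 0.49 |

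A yes/no variable cannot correlate perfectly with a many-valued score, so the second row is a ceiling. The first and last rows are the same patients with the same correlation; only division by four separates them.

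**When the consistency form fails.** With SD ratio k and r = 1, ICC = 2k/(1 + k²). This is below 0.5 when k² − 4k + 1 > 0, that is, when k > 2 + √3 = 3.73. With r = 0.7 the condition is k² − 2.8k + 1 > 0, so k > 1.4 + √0.96 = 2.38.

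**Constructed data, n = 100.** Thirty patients have domain sums 0, 1 or 2 (ten each) and seventy have 6 to 12 (ten each). Except where stated, the disorder is present exactly when the sum is 6 or more, so AUC = 1.00. ICCs are computed from the two-way mean squares:
- Item sum vs diagnosis: consistency 0.20, absolute agreement 0.07.
- Item mean vs the same diagnosis: 0.68 and 0.40.
- Items coded 1-4 instead of 0-3, sum vs diagnosis: consistency unchanged at 0.20, absolute agreement 0.03.
- Item sum vs an examination score that is an exact linear function of it (r = 1): range 0-3 gives 0.47 and 0.20; range 0-4 gives 0.60 and 0.29; range 0-12 gives 1.00 for both.
- Total 0-66 vs 0-4 affected domains, exact linear relation: 0.12 and 0.04.
- Kappa of the raw 0-12 score against a 0/1 diagnosis: 0.00. After both are dichotomised at the same point: 1.00.

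The AUC and rank correlation do not change under any of these linear rescalings.

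**The case against.** The mismatch of scales is inferred. The article speaks of domain scores on both sides, and a full protocol or analysis plan that is not shown may define them. If both were placed on one scale or standardised, most of the arithmetic above would lose its force: the ICC is 1.00 for a perfect linear relation on a shared 0-12 scale. The sum scoring, means and SDs are assumptions. This stands as a limit on the size of the problem. It does not rescue the choice of statistic, because the article itself names an agreement coefficient and a threshold for two different quantities. Any common scale would then be a convention, and the convention would decide the result.

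A reader might infer that the ICC cannot reach 0.5. The documents do not support that. In the consistency form at perfect correlation it fails only when the SD ratio exceeds 3.73; the disorder-count example reaches 0.60, and item-mean scoring exceeds 0.5 at a correlation of 0.7.

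A reader might also infer that the questionnaire will be rejected below 0.5. The text states a hypothesis and attaches no decision rule to it.

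Nor does objective 1 rest wholly on the ICC. ROC analysis of the domains and total is already planned and does not depend on scale, and AUC appears in the list of abbreviations. That is a real strength, although the stated purpose is to find cut-off points and no performance target is given.

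Finally, kappa may be meant for categories produced by those cut-offs. The wording allows this but does not say it, so the point on kappa is one of unclear specification, not demonstrated misuse.

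**Conclusion.** The concern holds in this form: as published, ICC > 0.5 is not a sound measure of criterion validity for the VIPD-Q, because the outcome can depend on unstated scoring and on the unstated ICC form. Under the assumed sum scoring against a yes/no disorder, the ceiling is 0.32 (consistency) or 0.14 (absolute agreement). With perfect discrimination in the constructed data, consistency ICC falls on either side of 0.5 (0.20 or 0.68) according to whether items are summed or averaged. These sizes rest on assumed coding, means, SDs and score distributions. The dependence on scale does not. The claim is that the hypothesis can be missed or met for reasons unrelated to validity, not that it will be. It deserves correction because no other numerical benchmark is given for the study's first aim.

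**What to change.** Before the objective 1 analysis:

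1. Make the planned ROC analysis the main validity measure. Report AUC with 95% CI for each domain and for the total, against the ophthalmologist's classification of that domain (and of any disorder, for the total). This also fits the questionnaire's purpose of selecting patients for referral.
2. Where the examination classification is graded, restate the > 0.5 hypothesis as a Spearman or polyserial correlation.
3. State beside that result that phase 2 takes patients from the top and bottom 30% of questionnaire scores, which inflates the correlation relative to all responders. The AUC from this sample needs the same caution.
4. Use kappa only after both sides are dichotomised, naming the questionnaire cut-off and the examination definition.
5. State how domain and total scores are formed, including the place of the six unassigned items.

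The cost is wording only. The data, patients and visits are unchanged.

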## Abstract

**Background:**

Visual disorders are common in Parkinson’s disease (PD) but their exact frequency and severity are unknown. Good visual functioning is crucial for patients with PD, because of their need to compensate for loss of automated motor control and their postural instability, forcing patients to guide their movements visually. Here, we describe the study design of a cross-sectional, multi-centre study aiming to: (1) validate the Visual Impairment screening questionnaire (VIPD-Q, which aims to identify PD patients who should be referred to an ophthalmologist for further assessment); (2) study the prevalence of visual disorders in PD; (3) study the severity and clinical impact of different types of visual disorders in PD; and (4) explore treatment options for ophthalmologic disorders in PD, as a basis for future guideline development.

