**Methods:**

This study consists of two phases. In phase one, 750 PD patients and 250 healthy controls will be recruited to complete the VIPD-Q. In phase two, a subgroup of responders (*n* = 100) (with the highest and lowest scores on the VIPD-Q) will be invited for an extensive neurological and ophthalmological assessment. The in-depth ophthalmologic examination will serve as the “gold standard” for validating the VIPD-Q. Moreover, these assessments will be used to study associations between visual disorders and clinical presentation, in order to gain more insight in their clinical impact.

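### ROC-optimal VIPD-Q cut-offs would be chosen and assessed in the same 100 patients with no optimism correction stated, so any accuracy quoted at them is too favourable on average

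*Protocol article*

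**What the plan says.** The questionnaire is a referral screen, "which aims to identify PD patients who should be referred to an ophthalmologist for further assessment" (Abstract, Background). The Abstract's Methods name the yardstick: "The in-depth ophthalmologic examination will serve as the" gold standard for its validation.

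That examination is done only in phase 2, where "a sample of 100 patients will be invited for a full clinical and ophthalmological assessment" (Patient collective and recruitment). The same section has the authors "aiming to include 70 patients with and 30 patients without visual impairment", the two groups being "patients scoring the highest 30% or the lowest 30% on the screening questionnaire". The OLVG site takes part in phase 1 only.

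In the Statistical analysis plan, examination results are sorted into disorders "within the domains of the VIPD-Q (ocular surface, intra- ocular, oculomotor and optic nerve". The main validity analysis is an ICC with Cohen's kappa and a hypothesised ICC above 0.5. The cut-offs are an addition: "we will calculate optimal cut-off points of the domains and total score of the VIPD-Q using the receiver operating characteristic (ROC". No criterion for the best cut-off and no internal or external validation step is stated. Confidence intervals of 95% are planned for all outcomes, and the software is SPSS 22.0.

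**The concern.** A cut-off picked because it gives the best trade-off in one sample has been fitted partly to that sample's chance features. Its accuracy in the same sample is therefore higher, on average, than in new patients drawn the same way. An ordinary 95% interval does not help, because it treats the cut-off as fixed beforehand.

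The design leaves no way round this by default: no described patient outside the 100 has the reference examination. For a referral screen, overstated sensitivity is the costly direction, since users would miss more disorders than the figures suggest.

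**Working it through.** **The plan's own figures.** The Netherlands contributes 10 + 20 = 30 and Austria 20 + 50 = 70, total 100. By score band, 10 + 20 = 30 low and 20 + 50 = 70 high. Four domains plus the total give five cut-offs. There is no precision or power calculation to reproduce.

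**Inputs from the article.** n = 100, drawn 70 from the top 30% and 30 from the bottom 30%. "The questionnaire includes 22 questions on visual problems", each with four answer levels, and Table 1 lists four questions per domain. With three steps per item (assumed equal scoring), there are 22 × 3 = 66 candidate cut-offs for the total and 4 × 3 = 12 for a domain.

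**Assumptions, not in the article.** AUC 0.7 or 0.8; prevalence in the source population 10, 20, 30 or 50%; normal scores with equal variance in patients with and without the disorder, separated by d = √2 × Φ⁻¹(AUC), that is 0.74 and 1.19; cut-off chosen by the largest sensitivity + specificity.

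**Calculation.** In each of 4,000 simulated samples per setting, find the best cut-off c, then compute

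optimism = [Se + Sp at c in the 100] − [Se + Sp at c in the population sampled the same way].

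Mean results in percentage points, planned 70/30 sampling (Se / Sp / sum; sums may differ by 0.1 from rounding):

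| AUC | Prevalence | Domain, 12 steps | Total, 66 steps |
|---|---|---|---|
| 0.7 | 10% | 7.4 / 0.9 / 8.3 | 11.9 / 1.4 / 13.3 |
| 0.7 | 20% | 4.6 / 1.2 / 5.8 | 6.9 / 2.3 / 9.2 |
| 0.7 | 30% | 3.3 / 1.9 / 5.2 | 4.9 / 2.9 / 7.9 |
| 0.7 | 50% | 2.0 / 2.8 / 4.8 | 2.8 / 4.0 / 6.9 |
| 0.8 | 10% | 6.5 / 0.9 / 7.4 | 9.6 / 1.5 / 11.0 |
| 0.8 | 20% | 3.6 / 1.4 / 5.0 | 5.6 / 2.4 / 8.0 |
| 0.8 | 30% | 2.4 / 1.7 / 4.1 | 3.7 / 2.9 / 6.5 |
| 0.8 | 50% | 1.5 / 2.5 / 3.9 | 2.0 / 3.3 / 5.3 |

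Repeating the simulation with fresh draws gives about 3 to 9 points for a domain and 5 to 13 for the total. The bias is positive in every setting.

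One simplification: patients are selected on the score being assessed. If selection is on the total, a domain score is selected less sharply. With no selection at all, the domain range is 4.3 to 12.0 points.

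**Effect of the remedy.** With the bootstrap correction described under the fix, the remaining overstatement is about 0 to 4 points.

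**Scale.** The half-width of an ordinary 95% interval for a sensitivity of 0.80 is 1.96 × √(0.8 × 0.2 / cases): 9.4 points with 70 cases, 14.3 with 30 and 24.8 with 10. The optimism is mostly smaller than this, but it always pushes the same way.

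**The case against.** **Silence is not absence.** This is a journal article, and the full protocol (version 3.0) is not shown. A reader might infer that the trial has no internal validation. The documents support only that none is stated. What stands regardless is that the article fixes the ROC search and confines the reference examination to 100 patients, so a correction is needed and ordinary intervals do not supply it.

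**Sensitivity and specificity are never named as outputs.** This is correct: the text promises cut-offs, and AUC appears only among the abbreviations. The point is therefore conditional on accuracy being quoted at the cut-offs. That is the natural product of a ROC analysis for a referral screen, but it is an inference.

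**Larger figures are tempting.** Overstatements of 14 to 16 points do arise for a 66-step score at 10% prevalence, but only with unselected sampling, which is not the plan. Nor does having five cut-offs inflate any one of them; the threshold search in a small sample does. That optic nerve disorders will be few is also unsupported, since no domain case numbers are given.

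**A larger bias lies elsewhere.** Under the same assumptions, sensitivity at the chosen cut-off exceeds that in all PD patients by 16 to 34 points, optimism included, and specificity shifts by −18 to +4. In the most extreme setting 33.6 − 11.9 = 21.7 points of the sensitivity excess come from selection on extreme scores. This objection stands in full: resampling within the 100 leaves that part untouched.

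**Conclusion.** The concern holds in a limited form. The stated design makes the same 100 patients both choose and assess each cut-off, and no correction is stated. Accuracy quoted at those cut-offs would be optimistic on average, by roughly 3 to 9 points of sensitivity plus specificity for a domain score and 5 to 13 for the total. These sizes depend on the assumed AUC, prevalence and scoring and on the maximum-sum criterion. They are largest for rare disorders, where most of the excess falls on sensitivity.

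This is a modest, cheaply corrected weakness in a secondary part of the validity analysis. It does not touch the ICC hypothesis. It also does not show that the questionnaire fails as a screen.

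**What to change.** - State the criterion that defines the optimal cut-off.
- Report optimism-corrected sensitivity and specificity for each score by bootstrap. Resample within the four score-band-by-centre groups (10, 20, 20 and 50 patients) and repeat the cut-off search in every resample. Take its sensitivity and specificity there minus those of the same cut-off in the actual 100, and subtract the mean difference from the apparent values.
- Give the bootstrap interval of each cut-off.
- Label the cut-offs provisional pending external validation.
- Say plainly that the correction applies only within the sampled top and bottom 30% and does not remove the bias from selecting on extreme VIPD-Q scores, which needs its own treatment.

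Setting a minimum sensitivity in advance, or giving no cut-off for domains with few cases, is optional and not part of the correction.

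The cost is a short script outside the SPSS menus and slightly less favourable accuracy figures. No new patients or measurements are needed. If the full protocol already contains such a step, one sentence saying so settles the statement of the method.
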